#### Adoption

We will assess adoption by measuring number and proportion of staff trained on each EBP, and how many and which types of staff delivered each EBP (representativeness), using administrative training records and administrative clinical data for each EBP.

#### Implementation fidelity

We will assess implementation strategy fidelity using the EBQI fidelity assessment tool [55]. The fidelity assessment tool draws from data collected from key stakeholder interviews, implementation facilitation logs, administrative documents, and weekly time diaries (described below). We will apply criteria to rate sites as high, medium, or low fidelity on the EBQI elements. Using the implementation facilitation logs, we will assess participation in the EBQI activities by frontline providers, staff, and leadership.

#### Maintenance

We assess maintenance by the extent to which EBPs are implemented after practice facilitation ends (e.g., about 18 months). We also plan to study if the EBPs are spread to other primary care teams within the site and to other sites within the healthcare system.

## Outcomes and data analyses

To analyze our primary outcome, receipt of each EBP among top 10th percentile high-risk patients during the 18-month implementation period (Reach), we will model uptake of both practices in our Concurrent Stepped Wedge Design as a multilevel hierarchical model with a repeated cross-sectional data structure in which sites are followed over time. In this design, the data structure includes patients at level 1 (where Reach, the main outcome of interest, in measured), nested within time at level 2, and nested within sites at level 3. The main predictors will be site implementation strategy assignment (EBQI-IC vs. EBQI-LC vs Usual Care) over time (measure as the number of quarter). We will first describe differences in trends using unadjusted analyses, then add covariates for patient characteristics (i.e., age, sex, Elixhauser comorbidity score [66]) and site-level covariates (i.e., number of unique patients served in primary care, rural vs urban). Secondary analyses of Reach will include models by key patient subgroups, including those hospitalized in the 90 days prior to the quarter examined, and models with an interaction term for assigned implementation strategy by EBQI fidelity level (as defined above), to examine how implementation strategy fidelity may have impacted Reach.

To analyze our secondary outcomes of care processes, patient experiences, provider experiences, and performance measures (Effectiveness), we will first model unadjusted trends in outcomes over time for each EBP, by site implementation strategy assignment. We will then model outcomes using two or three-level (depending on whether the metric is measured at the patient or site level) hierarchical models based on the concurrent Stepped Wedge Design using repeated cross-sectional data, adjusted for the same covariates included in the models for our primary outcome. In models of medication adherence, we will add covariates for medication regimen complexity, as indicated by total number of classes of medication prescribed for the condition of interest, and patient co-pay status. If we find differences in outcomes, we will perform mediation analyses that consider how Reach and EBP fidelity may have mediated outcomes [67].

To assess differences in adoption between EBQI-IC and EBQI-LC sites, we will use bivariate analyses to compare the number and proportion of staff trained on each EBP, and how many and which types of staff delivered each EBP. To assess differences in implementation strategy fidelity among sites, we will compare the number of sites with high, medium, and low fidelity on each element of EBQI, as well as overall fidelity to EBQI. Similarly, we will compare number of sites with overall high, medium, or low EBP fidelity among EBQI-IC vs EBQI-LC sites.

We will qualitatively assess the impact of contextual factors on implementation, using a matrix analysis approach [68] to explore a priori themes based on the interview guides, but also allow for emergent themes. Specifically, we will code and analyze interview data for core elements of the EBQI implementation strategy and for contextual features, intervention characteristics, and implementation infrastructure guided by the PRISM framework [33]. Two trained qualitative analysts will construct and validate the codebook [69]. Using this codebook, one analyst will code all interviews, and a second qualitative analyst will review all coding. After generating a report for all codes, they will use a matrix analysis approach [68] to populate a participant-by-theme matrix and create site level summaries for each theme to facilitate comparisons between EBQI-IC and EBQI-LC sites. To ensure rigor, summaries will also be reviewed, compared with the original data, and discussed by at least two analysts to reach consensus for any discrepancies. Finally, we will link this qualitative matrix with site-level implementation strategy and EBP fidelity measures to compare how specific contextual features, intervention characteristics, and implementation infrastructure impacted fidelity.

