#### Learning Collaboratives (LC)

Learning collaboratives are also widely used in healthcare settings and are an effective implementation strategy [30]. The RIVET learning collaboratives consists of external facilitators from the study team providing quality improvement training to QI participants from multiple sites in a group, and encourages interaction and collaboration among QI participants (e.g., providing feedback to each other). The effectiveness of learning collaboratives vary, but generally, they have demonstrated improvement in health professionals’ knowledge, problem-solving skills and attitude, and teamwork [53]. The mechanisms by which learning collaboratives may be effective include factors within an organization and factors between multiple organizations. In terms of factors within an organization, participation in learning collaboratives may increase staff confidence in using data to make decisions and to problem solve, increase accountability by making standards explicit, promote peer reflection, and facilitate teamwork, shared responsibility, and joint problem solving [53]. Mechanistic factors between organizations include normative pressure from peers, friendly competition, a platform for capacity building, and collaboration with other sites [53].

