### Site selection and eligibility

We will implement the EBPs at 16 primary care sites, targeting those with high ambulatory care-sensitive hospitalization rates. Each site will be implementing a single EBP. Implementation strategies are randomized by site. Site implementation consists of four overlapping cohorts of four sites (three randomized to LC and one to IC); all will undergo 18-months of RIVET facilitation (see Figure#1). Time periods without active implementation will serve as the usual care periods for EBQI strategies. Usual care sites will receive Office of Primary Care educational campaigns and dissemination of tools for high-risk patients among primary care teams. VHA regional leaders or VHA facility leaders will select the EBP for primary care sites to implement.

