### EBQI activities

We first engaged regional and local multidisciplinary stakeholders to discuss implementation of each EBP, such as the target patient population and the clinical staff who might perform the assessment, developing a “QI Roadmap.” QI training and practice facilitation spans 18 months of video calls with site clinical champions, selected by their facility leadership. Meetings are led by a trained RIVET external facilitator and include structured QI didactics, designing Plan-Do-Study-Act cycles, coaching, review of data, and developing structured action plans (Fig. 1). The RIVET implementation team provides quarterly data reports and regularly discuss next steps with the champions.

The same structured QI didactics are utilized for both LC and IC groups (Fig. 1). The IC sites participate in individual meetings with the clinical champions every month, on average. Learning collaboratives consist of three EBQI-LC sites that participate in monthly meetings. All sites randomly assigned to EBQI-LC participate in the same learning collaborative regardless of EBP (CACP vs MAA), as both EBPs involve the same goal, the same target population, in the same clinical setting, similar to prior initiatives [17, 31, 55].

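### The primary Reach model stops at site, although LC is delivered to four three-site collaboratives, so LC and IC–LC standard errors are too small if collaboratives share any variance

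*Protocol article*

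**What the plan says.** Under Site selection and eligibility, the Protocol article gives the size, "We will implement the EBPs at 16 primary care sites", the unit, "Implementation strategies are randomized by site", and the structure, "four overlapping cohorts of four sites (three randomized to LC and one to IC". That is 12 LC and 4 IC sites.

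Under EBQI activities: "Learning collaboratives consist of three EBQI-LC sites that participate in monthly meetings". The same section adds: "All sites randomly assigned to EBQI-LC participate in the same learning collaborative regardless of EBP". Read with three LC sites per cohort, this means one collaborative per cohort, mixing the two practices where sites chose differently, and four collaboratives in all.

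Under Learning Collaboratives (LC), the mechanisms said to act between organisations are "normative pressure from peers, friendly competition, a platform for capacity building, and collaboration with other sites".

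Under Outcomes and data analyses, the model for Reach has patients at level 1, "nested within time at level 2, and nested within sites at level 3". Its predictors are given as: "The main predictors will be site implementation strategy assignment (EBQI-IC vs. EBQI-LC vs Usual Care) over time (measure as the number of quarter". The site-level covariates are clinic size and rurality. No collaborative level, cohort term or robust variance is named.

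**The concern.** A strategy that works by making three sites influence each other should leave their outcomes correlated. A model whose top level is site treats the 12 LC sites as 12 independent replications of LC, although LC as a strategy is replicated only four times. Any variation between collaboratives, such as a cohesive group against a disengaged one, is then counted as if it had been seen 12 times over. IC sites have no such grouping, so the dependence lies in one arm only.

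IC against LC is the question the trial exists to answer, and the Discussion says the answer will guide wider implementation. An interval for that contrast that is too narrow could lead to one strategy being preferred on chance differences between four groups.

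**Working it through.** **Counts.** 4 cohorts × (3 LC + 1 IC) = 16 sites, which reproduces the stated total: 12 LC, 4 IC, 4 collaboratives. The document gives no intraclass correlation, alpha, power or standard error, so every correlation below is an assumption and is shown as a range.

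**Closed form on site means.** Let s² be the between-site variance and r the share of it common to a collaborative.
- LC mean: modelled s²/12, true s²(1+2r)/12. Ratio 1+2r.
- IC mean: s²/4 in both cases.
- IC–LC: modelled s²(1/4+1/12) = s²/3, true s²[1/4+(1+2r)/12] = s²(4+2r)/12. Ratio 1+r/2.

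| r | LC variance ratio | LC SE ratio | 12 LC sites act as | IC–LC variance ratio | IC–LC SE ratio |
|---|---|---|---|---|---|
| 0.1 | 1.20 | 1.10 | 10.0 | 1.05 | 1.02 |
| 0.2 | 1.40 | 1.18 | 8.6 | 1.10 | 1.05 |
| 0.3 | 1.60 | 1.26 | 7.5 | 1.15 | 1.07 |
| 0.5 | 2.00 | 1.41 | 6.0 | 1.25 | 1.12 |

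The same correlation also shrinks the observed spread among LC sites. Of the 66 pairs of LC sites, 12 share a collaborative, so the expected LC sample variance is s²(1−2r/11) and the pooled variance on 14 df is s²(1−r/7). The true-to-estimated SE ratio for IC–LC is therefore √[(1+r/2)/(1−r/7)]: 1.06 at r=0.2 and 1.16 at r=0.5.

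**Simulated type I error for IC–LC** (nominal 5%, site means, t on 14 df, no cohort variance): 5.0% at r=0, about 6.4% at r=0.2, and 9.2% to 9.4% across repeated runs at r=0.5.

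**Cohort.** Every cohort contributes three of the 12 LC sites and one of the four IC sites, so a shared cohort effect has the same average in both arms and cancels from IC–LC. Leaving it out only inflates the estimated variance. With no collaborative effect, type I error is 4.2% at a cohort share of 0.1 and 2.7% at 0.3. With both shares at 0.1 it is 4.8%. With cohort variance of 0.25 added to unit site variance it is 3.5% at r=0 and 4.6% at r=0.2.

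Adding cohort without the collaborative removes this offset. With z-tests on both sides, and no cohort variance, error rises from 8.7% to 10.7% at r=0.2 and from 12.1% to 17.5% at r=0.5. About 2 to 3 points of the two lower figures come from using z rather than t.

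**Stepped-wedge version.** Assumed: fixed quarter effects, a site intercept, two baseline quarters, six active quarters (18 months), none afterwards, cohorts 1 to 3 quarters apart, site variance 1, remaining site-quarter variance 0.3, and a collaborative effect present only in active LC quarters.
- With variance components held fixed and collaborative variance at 0.05 to 0.3 of site variance, the true-to-modelled SE ratio is 1.14 to 1.85 for LC–IC and 1.15 to 2.11 for LC against usual care. These are upper-range figures, because a fitted model absorbs part of the extra variance.
- With components re-estimated by REML in each simulated trial, LC–IC type I error is about 5% with no collaborative variance, 8–10% at 0.05 of site variance, 11–16% at 0.1 and 17–21% at 0.2.
- A cohort effect alone leaves the LC–IC ratio at 1.000.

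The effect is larger here because the model gains precision from change within sites, and the collaborative effect arises exactly when that change is measured.

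**Within-cohort check.** Taking one IC site against the mean of its collaborative in each cohort, four differences on 3 df, type I error stays at about 5% in every site-mean scenario.

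**The case against.** The strongest reply has four parts.

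1. *The size is unknown.* True. No correlation is given. On site means the IC–LC standard error is short by only 1–7% for r from 0.05 to 0.3 by the closed form, and cohort variance can cancel the inflation. A reader might infer that the false-positive rate certainly exceeds 5%. The document does not support that; the statement is conditional on positive collaborative variance. What stands is that the protocol itself names the mechanism that would produce it.

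2. *Cohort is also missing, so the harm is double.* This is the other tempting inference, and it is wrong for IC–LC. Allocation is within cohort, so omitting cohort is conservative or neutral for that contrast.

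3. *An article leaves such detail to the analysis plan.* This is fair for the reference distribution and small-sample corrections, so no excess due to z instead of t is held against the plan. It does not cover the hierarchy, which is set out level by level and ends at site.

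4. *The stepped-wedge figures rest on invented variances and a linear model.* They do. They show direction and possible size, and are not a forecast for this trial.

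**Conclusion.** The concern holds in conditional form. The stated hierarchy conflicts with the way LC is delivered. With any positive collaborative-level variance, the standard error for LC is too small, and so is the one for IC–LC unless unmodelled cohort variance offsets it. On site means the IC–LC error rate is modestly inflated, to about 6.4% at r=0.2 and 9.4% at r=0.5 (14-df t-test, no cohort variance). In the planned stepped-wedge analysis the inflation can be larger at smaller correlations, under the assumptions listed. The omission of cohort is not part of the fault for IC–LC. The point rests on four collaboratives of three sites, one per cohort, and on values of r that the document does not supply.

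**What to change.** Amend the primary model before analysis:

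- Add a collaborative-level random effect for LC sites during their active quarters, in a partially nested form with each IC site as its own group.
- Use small-sample degrees of freedom that reflect four collaboratives rather than 12 LC sites.
- Support the IC–LC contrast with a prespecified within-cohort analysis: one IC site against the mean of its collaborative, four pairs, 3 df.
- If a cohort term is wanted, add it only together with the collaborative effect, since cohort alone makes the inflation worse.

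A re-randomisation test over the 4⁴ = 256 within-cohort allocations is not a substitute. Sites that share a collaborative effect are not exchangeable with the IC site, and in simulation the test's type I error was about 7% at r=0.2 and 13% at r=0.5.

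The cost is analysis work only, with no new sites or data. Intervals will widen: in the strictest version the critical t is 3.18 on 3 df against 2.14 on 14 df. The collaborative variance will be weakly estimated from four groups, and it separates from cohort variance largely through the four IC sites. For that reason the within-cohort analysis should be reported beside the model.

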**Methods:**

We will recruit and randomize 16 sites to either EBQI-IC or EBQI-LC to implement one of the EBPs, chosen by the site. Each site will have a site champion (front-line staff) who will participate in 18 months of EBQI facilitation.

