**Discussion:**

Our study will identify which implementation strategy is most effective overall, and under various contexts, accounting for unique barriers, facilitators, EBP characteristics, and adaptations. Ultimately this study will identify ways for primary care clinics and teams to choose implementation strategies that can improve care and outcomes for patients with complex healthcare needs.

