### EBQI Implementation strategies

The high-Risk VETeran (RIVET) Program will compare two variants of Evidence-Based Quality Improvement (EBQI)—practice facilitation through Individual Consultation (IC) or through Learning Collaboratives (LC) to determine which of the two is the most effective and less costly implementation strategy and explore which is better suited for which contexts.

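### Secondary Reach analyses are fitted by patient subgroup; one model with a strategy-by-subgroup interaction would show whether the IC-LC difference varies between patient groups

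*Protocol article*

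**What the plan says.** The section Outcomes and data analyses describes a multilevel model for Reach with patients within time within sites. For the main comparison: "The main predictors will be site implementation strategy assignment (EBQI-IC vs. EBQI-LC vs Usual Care) over time". It then turns to secondary work: "Secondary analyses of Reach will include models by key patient subgroups, including those hospitalized in the 90 days prior to the quarter examined". The same sentence adds "models with an interaction term for assigned implementation strategy by EBQI fidelity level (as defined above". So the text gives fidelity an interaction term, and gives patient subgroups models fitted by subgroup.

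Two design facts bear on the point. The abstract says "We will recruit and randomize 16 sites to either EBQI-IC or EBQI-LC", and Site selection and eligibility describes "four overlapping cohorts of four sites (three randomized to LC and one to IC". That makes 4 × 1 = 4 IC sites and 4 × 3 = 12 LC sites.

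The article states no significance level, power, effect size, intraclass correlation or subgroup share.

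**The concern.** A model fitted within one patient group answers the question of how the strategies compare in that group. It contains no estimate of how the comparison differs from that in the remaining patients. Recently hospitalized patients are presumably the smaller group, so their IC-LC estimate would be less precise. With the same true effect in both groups, one result can pass the significance threshold and the other miss it. A reader could take this to mean that the better strategy depends on the type of patient.

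At stake is the interpretation of a secondary analysis. The authors already use an interaction term where they want to know whether the strategy effect depends on fidelity. The same tool suits the patient-group question, and it suits this design well. Every IC-LC contrast within a subgroup rests on only 4 IC sites and carries their between-site noise. The difference of that contrast between patient types is formed within sites, so site effects common to both types cancel.

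**Working it through.** The plan gives no figure on this point, so there is none to reproduce. What follows is an illustration, and every input is an assumption.

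**Inputs (assumed).**
- Two-sided 5% tests, so the critical value is 1.96.
- Two complementary subgroups with shares f and 1 − f, with f = 0.5, 0.2 or 0.1.
- The same true IC-LC effect in both.
- The overall estimate has variance T + S = 1, where T comes from site effects shared by both subgroups and S is the rest. T = 0, 0.5, 0.8 or 0.95.

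**Formulas.**
- Subgroup variances: v1 = T + S/f and v2 = T + S/(1 − f).
- Correlation of the two estimates: T/√(v1·v2).
- Expected z in each subgroup: d/√v1 and d/√v2. For 80% overall power, d = 1.96 + 0.84 = 2.80.
- Discordance (exactly one subgroup significant): p1 + p2 − 2·P(both significant), from the bivariate normal distribution.

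**One case in full** (f = 0.2, T = S = 0.5).
- v1 = 0.5 + 0.5/0.2 = 3.0 and v2 = 0.5 + 0.5/0.8 = 1.125.
- Correlation = 0.5/√(3.0 × 1.125) = 0.27.
- Expected z = 2.80/√3.0 = 1.62 and 2.80/√1.125 = 2.64.
- Subgroup powers are 0.37 and 0.75, and the discordance is 0.505.

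**Discordance at 80% overall power, no true heterogeneity.**

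| Smaller-group share | T = 0 | T = 0.5 | T = 0.8 | T = 0.95 |
|---|---|---|---|---|
| 0.5 | 0.500 | 0.368 | 0.221 | 0.103 |
| 0.2 | 0.608 | 0.505 | 0.328 | 0.142 |
| 0.1 | 0.683 | 0.620 | 0.467 | 0.217 |

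The range is about 10% to 68%. Over the same grid it is 14% to 47% at 50% overall power, 7% to 74% at 90%, and 4% to 10% with no strategy effect at all.

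Precision and correlation are linked here. Since T cannot exceed v2, the correlation cannot exceed √(v2/v1), the ratio of the standard errors. The two should not be varied independently.

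**The interaction.** The variance of the difference between the subgroup effects is v1 + v2 − 2T = S/f + S/(1 − f) = S/[f(1 − f)]. T drops out, which is the within-site property. A single two-sided 5% test of this difference gives a false signal of heterogeneity in 5% of trials, whatever the main effect, provided the model fits.

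The price is precision. In the worked case the variance is 0.5/(0.2 × 0.8) = 3.125, a standard error of 1.77 times that of the overall effect. Over the grid the multiple runs from 0.45 (f = 0.5, T = 0.95: √(0.05/0.25)) to 3.33 (f = 0.1, T = 0: √(1/0.09)).

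**The case against.** The strongest reply has four parts.

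*This is an article, and details belong elsewhere.* The full protocol and any SAP are not shown. A complete list of subgroups, an exploratory label and the exact form of testing may be there. This stands. The open list and the missing label are not findings. What remains is the form of model that the article does state.

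*No rule says subgroup p-values will be compared.* This also stands. A reader might infer that the trial intends to declare heterogeneity from significance in one group and not in another. Nothing in the document says so. Models by subgroup could serve simply to describe Reach in a priority population, which needs no heterogeneity test. Misreading is foreseeable, but it is not planned.

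*The link to the trial's aims is weak.* A reader might connect the subgroup models to the abstract's "Our study will identify which implementation strategy is most effective overall, and under various contexts" and contrast it with "explore which is better suited for which contexts" in EBQI Implementation strategies. The abstract's sentence continues with barriers, facilitators, features of the practice and adaptations, and the main Discussion does much the same. Contexts there are organizational. No claim about patient groups is announced, so no change to the abstract follows from this point.

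*The frequency is unknown.* Correct. Because strategy is assigned by site, the subgroup estimates share site effects. When those dominate, discordance is much lower: 0.14 at 80% power, a 20% subgroup and T = 0.95. To say that the subgroup results will often mislead goes beyond the document. Nor does an interaction term cure multiplicity, since several interaction tests would also accumulate error. The point does not rest on multiplicity.

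**Conclusion.** The point holds in a limited form. The stated method, models by patient subgroup, cannot show whether the IC-LC difference varies between patient groups, and the same sentence already uses the tool that can.

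The size is illustrative only: discordant significance of about 10% to 68% at an assumed 80% overall power with identical true effects, against 5% for one interaction test. It rests on assumed power, subgroup share, site-level variance and a 5% level, none of which the article supplies. With no strategy effect and dominant site variance, discordance can fall to 4%, so the gain is not uniform.

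The analysis is labelled secondary and the primary Reach comparison is untouched. This is a cheap improvement, not a threat to the trial's main conclusion.

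**What to change.** Replace the models by patient subgroup with one Reach model on all eligible patients. It would hold the strategy terms, the subgroup indicator (for example, admitted in the preceding 90 days: yes or no), the strategy-by-subgroup interaction and time trends that may differ by subgroup. Report the interaction estimate for IC versus LC with its confidence interval, and the effects within each patient group derived from the same model. If the purpose is only to describe Reach within a group, say so.

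The cost is a wording change and extra model terms on data already to be collected. The downside is that the interaction estimate will be imprecise, so statements about patient groups will be weaker than separate models might appear to allow.
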